# STUDY DESIGN

## Overall Design

This is a randomized controlled trial (RCT) of Skills to Enhance Positivity (STEP) vs. Enhanced Treatment as Usual (ETAU). It is hypothesized that those randomized to STEP, compared to ETAU, will have lower rates of suicide events, active SI, and depression over the 6-month follow-up period (primary endpoint), and over 12 months of follow-up (secondary endpoint). Recruitment will occur at three sites, Boston Children’s Hospital, Butler Hospital, and Bradley Hospital. Eligible individuals who consent to participate will be randomly assigned to either STEP or ETAU in a 1:1 allocation after the baseline assessment. Co-I [name] will prepare a stratified [by study site, history of SB (yes/no), and sexual or gender minority (yes/no)} randomization schedule using random blocks and provide this to our REDCap administrator; study staff will not have access to randomization tables). Research staff will be able to obtain assignments in real time once consent and stratification variable information are recorded. We use random block sizes to prevent guessing of pending treatment assignments.

The study intervention, Skills to Enhance Positivity (STEP), is an adjunctive psychosocial intervention that involves 4 in-person sessions during a participant’s inpatient admission, followed by three months of text or email messaging for mood monitoring and skills delivery. (If participant has a shorter length of stay or is discharging early, the STEP sessions may be shortened so that the intervention can be delivered prior to discharge). The sessions and skills delivered via the text or email messages focus on the functions of positive affect and ways to bring greater attention to and awareness of positive emotions and experiences on a daily basis. Four videos with content derived directly from the treatment manual will be used to support the delivery of the STEP skills that are covered in the in-person sessions.

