## Scientific Rationale for Study Design

The study design is an RCT comparing the study intervention to an enhanced treatment as usual condition. All participants receive equivalent inpatient care with the exception of receiving either STEP sessions or. TAU therapy sessions, depending on the condition to which they are designed. STEP participants will be pulled from regular therapeutic programming for their 4 STEP sessions (while ETAU will be in therapy sessions). After discharge, ETAU get prompts to remind them of their safety plan or practice a Healthy Habit with the same frequency as STEP participants. Both conditions receive the exact same assessments and the passage of time is equivalent. Therefore, we do not anticipate any problems associated with the control group in light of participants’ risk for suicidal behavior, as they will continue to receive ongoing treatment on the inpatient unit and are able to engage in outpatient treatment after discharge.

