The comparison condition consists of treatment as usual on the unit which is enhanced by asking participants to take a photo of their safety plan to store on their phone, and to ask participants to store phone numbers of supportive contacts on their phone. Participants will receive texts or emails on a daily basis for 30 days with reminders to check their safety plan and other healthy habit reminders. This procedure helps control for contact time by equating the two conditions. Unlike the STEP condition they will not receive the mood monitoring questions or positive affect skills as these are conceptualized as part of the study intervention. ETAU participants will be placed on a tapered schedule of receiving alerts 3 times per week for an additional 60 days. After 3 months, they will no longer receive alerts.

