## Participant Discontinuation/Withdrawal from the Study

Participants are free to withdraw from participation in the study at any time upon request.

An investigator may discontinue a participant from the study for the following reasons:

- Significant study intervention non-compliance, i.e. with respect to the individual sessions, unless varying compliance is an aspect of the study objectives
- Lost-to-follow up; unable to contact subject (see **Section 7.3, Lost to Follow-Up**)
- Any event or medical condition or situation occurs such that continued collection of follow-up study data would not be in the best interest of the participant or might require an additional treatment that would confound the interpretation of the study
- The participant meets an exclusion criterion (either newly developed or not previously recognized) that precludes further study participation

The reason for participant discontinuation or withdrawal from the study will be recorded on the Case Report Form (CRF). Subjects who sign the informed consent form and are randomized but do not receive the study intervention may be replaced. Subjects who sign the informed consent form, and are randomized and receive the study intervention, and subsequently withdraw, or are discontinued from the study, will not be replaced.

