handled with multiple imputations, with assumptions checked with sensitivity analyses (76), is pre-specified (as are all aspects of our analysis plan). We will adhere to intent-to-treat principles, and all aspects of data analysis will be pre-specified as reflected in this proposal, and with modification following proposal review and discussions with program and our Data Safety and Monitoring Board. Preliminary analyses will include descriptive statistics to examine the distributional and psychometric properties of the variables (e.g., normality, internal consistency). Variables will be transformed to better approximate normality if this is necessary given the observed distribution and the assumptions of the analysis model. We will also examine post-inclusion attrition by comparing study completers to dropouts on sociodemographic, baseline data, and psychotropic medication usage to determine if they differ systematically. We will examine the success of the stratified randomization by examining between-group differences at baseline. Preliminary analyses may also include analyses of adverse events, the progress of recruitment and retention, and data processing and quality markers as the study progresses. Daily mood monitoring data is not included in outcome analyses because it is conceptualized as part of this adjunctive intervention and only collected in one condition.

Missing data. To accommodate attrition and other sources of missingness, we will utilize the method of multiple imputation by chained equations. At least 50 replicates of each missing value will be generated for inclusion in analyses. This method can accommodate clustering of repeated measures at the level of the. We have previously used these methods in successful analyses of trials of exercise interventions.

Statistical computing. Modeling will be performed using Stata (Stata Corp, College Station, TX, version 16.2 or higher) and R software (R Foundation for Statistical Computing, Vienna, Austria, version 4.0 or higher) and Mplus (version 8.4 or higher, Muthen & Muthen, Los Angeles, CA). Analyses and reporting will be executed and archived to ensure full replicability and reproducibility by analysts at Brown University, under the direction of the project methodologist, [name].

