### Quality Assurance and Quality Control

Each clinical site will perform internal quality management of study conduct, data collection, documentation and completion. All sites will follow a common quality management plan to be developed in advance of study start up.

Quality control (QC) procedures will be reviewed annually and include:

**Informed consent ---** Study staff will review both the documentation of the consenting process as well as a percentage of the completed consent documents. This review will evaluate compliance with GCP, accuracy, and completeness. Feedback will be provided to the study team to ensure proper consenting procedures are followed. Study staff obtaining consent will be required to get a secondary quality assurance check from a different member of the research team prior to working with the participant, to verify completion of every section of the consent document and to review any potential errors. Once the consent is completely and accurately completed, it will be noted in the study tracking system.

**Source documents and the electronic data ---** Data will be initially captured on source documents (see **Section 10.1.9, Data Handling and Record Keeping**) and will ultimately be entered into the study database. To ensure accuracy site staff will compare a representative sample of source data against the database, targeting key data points in that review.

**Intervention Fidelity** — Consistent delivery of the study interventions will be monitored throughout the intervention phase of the study. Procedures for ensuring fidelity of intervention delivery are described in **Section 6.2.1, Interventionist Training and Tracking**.

**Protocol Deviations** – The study team will review protocol deviations on an ongoing basis and will implement corrective actions when the quantity or nature of deviations are deemed to be at a level of concern.

**Text Messaging**. The functioning of the text messaging program will be checked on a monthly basis, with respect to both functionality and data collection.

Should independent monitoring become necessary, the MPIs will provide direct access to all trial related sites, source data/documents, and reports for the purpose of monitoring and auditing by the sponsor/funding agency, and inspection by local and regulatory authorities.

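### The protocol lets randomized participants who do not receive the study intervention be replaced, mainly a STEP-arm condition, without saying they stay in follow-up and in the intent-to-treat analysis

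*Protocol*

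**What the plan says.** The section Participant Discontinuation/Withdrawal from the Study contains the rule: "Subjects who sign the informed consent form and are randomized but do not receive the study intervention may be replaced". Its next sentence bars replacement once the intervention has been received. The same section lets an investigator discontinue a participant from the study for significant non-compliance with the individual sessions.

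Three places show what the term study intervention means. Overall Design: "The study intervention, Skills to Enhance Positivity (STEP), is an adjunctive psychosocial intervention that involves 4 in-person sessions". Scientific Rationale for Study Design: "The study design is an RCT comparing the study intervention to an enhanced treatment as usual condition". Administration and/or Dosing says of the ETAU group that "they will not receive the mood monitoring questions or positive affect skills as these are conceptualized as part of the study intervention". There is looser usage too. Quality Assurance and Quality Control says "Consistent delivery of the study interventions will be monitored throughout the intervention phase of the study", and the study schema also uses the plural.

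Statistical Considerations states: "We will adhere to intent-to-treat principles, and all aspects of data analysis will be pre-specified as reflected in this proposal". The section on discontinuation of the study intervention keeps a participant who stops the intervention, but not the study, in all later scheduled assessments.

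**The concern.** Whether a participant received the intervention is known only after randomization, and staff know the arm when it becomes known. STEP has four staff-delivered sessions that can fail to happen. ETAU is usual unit care plus a stored safety plan, stored contacts and automated messages, so non-receipt is much harder to trigger there.

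The protocol does not give the reasons for never starting. Early discharge, refusal and clinical deterioration are plausible ones, and each could be related to the risk of a suicidal event. If such people were removed from STEP alone, the arms would no longer be comparable as randomized, and every primary comparison would be exposed.

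This is a conduct rule and not only an analysis rule. If staff stop following a replaced participant, that person's interview outcomes at 3, 6 and 12 months are not collected, and no later analysis plan can recover them. Records of emergency visits and admissions could fill only part of the gap.

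**Working it through.** **1. What the text settles and what it leaves open.**
- Who qualifies: no arm is named. Read literally, no ETAU participant ever receives the study intervention, so all of them would be replaceable, which cannot be meant. The sensible reading is STEP allocations with no session. The plural usage allows a wider reading in which an ETAU participant who received no messages also qualifies.
- What counts as receiving: not defined. Justification for Intervention sets a minimum participation (one session plus any messaging), but the replacement rule does not refer to it.
- What happens to the replaced person: not stated. The rule sits among provisions on leaving the study. The promise of continued assessment covers people who stop the intervention but remain in the study, so it does not clearly cover a never-starter.
- How the replacement enters: not stated. The only allocation route described is the concealed, stratified, blocked schedule in REDCap.

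**2. Does any planned number depend on replacement?** Target recruitment is 216, and power uses 162, or 81 per group (216 × 0.75 = 162). For 38% against 17%, the protocol states 80% power. Its printed formula, with p0 = 0.275 and an assumed two-sided alpha of 0.05, gives Φ(√(81 × 0.21² / (0.275 × 0.725) / 2) − 1.96) = Φ(2.993 − 1.960) = 84.9%. A continuity-corrected version gives 81.1%, close to the stated figure. Neither 216 nor 162 relies on replacement.

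**3. Size of the bias if replaced STEP participants were dropped.** Inputs: no true effect, and an event rate of 38% in both arms as randomized (the protocol's ETAU rate). Assumed: a fraction f of STEP never starts, with event rate r. The remaining STEP rate is s = (0.38 − f·r)/(1 − f), and the false difference is d = 0.38 − s. With n = 81 per arm, p̄ = (0.38 + s)/2, SE0 = √(2p̄(1 − p̄)/n) and SE1 = √((0.38 × 0.62 + s(1 − s))/n), the type I error is Φ((d − 1.96·SE0)/SE1) + Φ((−d − 1.96·SE0)/SE1).

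Example, f = 10%, r = 1.5 × 0.38 = 0.57: s = (0.38 − 0.057)/0.90 = 0.359; d = 2.1 points; SE0 and SE1 both about 0.0758; type I error = 0.046 + 0.013 = 5.9%.

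| f | r | False difference (points) | Two-sided type I error |
|---|---|---|---|
| 2% | 0.50 to 0.76 | 0.2 to 0.8 | 5.0% to 5.1% |
| 5% | 0.475 (1.25 × 0.38) | 0.5 | 5.05% |
| 5% | 0.50 to 0.76 | 0.6 to 2.0 | 5.1% to 5.8% |
| 10% | 0.57 (1.5 × 0.38) | 2.1 | 5.9% |
| 10% | 0.50 to 0.76 | 1.3 to 4.2 | 5.4% to 8.6% |
| 15% | 0.50 to 0.76 | 2.1 to 6.7 | 5.9% to 14.5% |

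If everyone is followed and analysed as randomized, d = 0 whatever f is.

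**4. Which f is plausible?** Administration and/or Dosing reports that all pilot participants were started on the unit. Taking that as 0 of the 26 STEP participants, the exact one-sided 95% upper limit is 1 − 0.05^(1/26) = 10.9%. The best guess is therefore near zero, and the 15% row is a stress case.

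**The case against.** The strongest reply is that the protocol commits to intent-to-treat and that the replacement sentence does not contradict it. "We will adhere to intent-to-treat principles" can stand beside the rule if replacing someone only means enrolling one more participant while the first stays in the assigned arm. That is correct. A reader might infer that the rule breaks intent-to-treat, but the text never says a replaced participant leaves follow-up or analysis.

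A reader might also infer that STEP non-starters are swapped for STEP starters outside the blocked schedule. The documents do not support that either. No other route of entry is described, and a newcomer randomized through REDCap could be assigned to either arm.

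Nor is it established that only STEP can trigger the rule. That is the natural reading, but the plural usage and the study-delivered ETAU components leave room for another.

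Finally, sessions may be compressed for short stays, which should keep never-starting rare, and replacement is barred once the intervention has been received.

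What remains is that the rule is open on each of these points. Its position among the withdrawal provisions, next to a session-based ground for leaving the study that can apply only to STEP, makes the harmful reading available to staff who know the allocation.

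**Conclusion.** The point holds as an unreconciled conduct rule. It permits a departure from intent-to-treat that would fall mainly on STEP; it does not prescribe one.

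The bias is zero if all randomized participants are followed and analysed as assigned. If never-starters were dropped, 5% to 10% of them at 1.25 to 1.5 times the average event rate would produce a false difference of about 0.5 to 2.1 points and a two-sided type I error of about 5.05% to 5.9%. The never-starter fractions and risk ratios are assumptions, as is the 5% two-sided alpha, for which the protocol gives no number. With no never-starters in the pilot, the real effect is probably small.

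The reason to act is that the loophole costs almost nothing to close, while outcomes lost through it could not be fully recovered.

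**What to change.** Delete the replacement sentence. Alternatively, keep it and add two statements:
- Every randomized participant is followed at 3, 6 and 12 months and analysed in the assigned arm, whether or not any session was received.
- Any added enrolment goes only through the normal stratified blocked schedule.

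Report by arm the number randomized, and for STEP the number with no session. Reconcile the session non-compliance ground for leaving the study with the continued-assessment provision for people who stop the intervention and with the intent-to-treat commitment.

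Cost: a sentence or two by amendment, with no change to 216 or 162. The downside is some dilution from never-starters kept in STEP. If they had the 38% rate and starters 17%, the STEP rate would be 0.38f + 0.17(1 − f). Power at 81 per arm (normal approximation, no continuity correction) would fall from 85.6% to 84.0% at f = 2%, 81.3% at 5% and 76.4% at 10%. At pilot-like rates the loss is slight.

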## Lost to Follow-Up

A participant will be considered lost to follow-up if he or she fails to return for 3 scheduled follow-up assessment visits and study staff are unable to contact the participant after at least 3 attempts.

The following actions must be taken if a participant fails to return to the clinic for a follow up assessment visit:

- The site will attempt to contact the participant, reschedule the missed visit within two weeks, counsel the participant on the importance of maintaining the assigned visit schedule and ascertain if the participant wishes to and/or should continue in the study
- Before a participant is deemed lost to follow-up, the investigator or designee will make every effort to regain contact with the participant (where possible, 3 telephone calls and, if necessary, a certified letter to the participant’s last known mailing address or local equivalent methods). These contact attempts will be documented in the participant’s study file.
- Should the participant continue to be unreachable, he or she will be considered to have withdrawn from the study with a primary reason of lost to follow-up.

# STUDY ASSESSMENTS AND PROCEDURES

## Endpoint and Other Non-Safety Assessments

Please refer to Section 1.3, Schedule of Activities to see list of assessments, assessment modality, and timetable of specific administrations. Of note, guardians will be mainly reporting on adolescent thoughts, feelings, and behaviors for the assessment areas described below.

Demographics and Background Variables. Routine demographic variables will be collected. We will ask questions from the overview of the *Kiddie Schedule for Affective Disorders and Schizophrenia – Present and Lifetime version (KSADS-PL*)(52) to assess for current living situation, legal involvement, history of abuse, family psychiatric history, treatment history and payor information. Self-report forms will be used to ask about sexual and gender identity.

Suicidal Events. Suicidal events (operationalized as a composite score of suicide attempts and inpatient hospital/ED admissions)(42) will be assessed with the *Columbia-Suicide Severity Rating Scale* (50) and the *Child and Adolescent Services Assessment* (53). The C-SSRS assesses the range of suicidal behavior including preparatory acts, aborted attempt and interrupted attempt, and passive and active SI, as well as intensity of ideation. At f/u, suicidality since the last assessment and in the prior week will be assessed. The CASA is a semi-structured interview that obtains information about service use across multiple sectors (e.g., juvenile justices, schools). Adequate reliability has been demonstrated for this measure (ICCs=.74-.76)(53). Interviews will be administered at baseline, 3-, 6-, and 12-months f/u, with the 6-month follow-up as our primary outcome (Ho1A). The CASA will be used to systematically assess ED evaluations and psychiatric hospitalizations.

Suicidal Ideation. Active SI will also be assessed using the C-SSRS; specifically, we will assess active SI, operationalized by a score of 3 or higher on the suicide ideation questions of C-SSRS, using their highest level of ideation during the worst week of the f/u interval. We will also obtain weekly ratings of SI using the methodology of the *Longitudinal Interval Follow-Up Evaluation* (LIFE)(54), at the 3-, 6-, and 12 month f/u’s. The LIFE format asks participants to rate their level of SI in the preceding interval on a 6-point psychiatric status rating (PSR) scale. This methodology, which yields weekly scores, as applied to the assessment of SI in adolescents has been successfully implemented in at least three NIMH-funded studies for which MPI [name] was a PI (K23MH069904, MH090137, MH059929). Our data from adolescents admitted to the Butler adolescent unit and followed for 6 months after discharge (K23MH069904) demonstrate a good range of variability in SI PSR scores (e.g., 20% clinically significant SI; 36% no weeks clinically significant SI, 6% chronic, unremitting, high levels of SI for all weeks of f/u). We will also administer the Suicide Ideation Questionnaire, a 30-item self-report instrument with good psychometric properties in adolescents.

Diagnostic / Symptom Rating Scales. Depression will be assessed by the *Beck Depression Inventory (BDI-II)* (39) administered to both adolescent and parent (about teen). The BDI-II is a widely used 21-item measure with excellent psychometric properties (55), and also validated in Spanish. Cronbach’s α in the pilot sample was 0.90 in adolescents and 0.89 in adults. Alcohol use will be assessed using the Alcohol Use Disorder Identification Test (AUDIT) and drug use will be assessed using the Drug Use Disorder Identification Test (DUDIT). Other symptom rating scales include the Borderline Evaluation of Severity Over Time (BEST) and the Columbia Impairment Scale (CIS). All are self-reports and assessments will be administered at baseline, 3-, 6-, and 12-months f/u.

Implicit Positive and Negative Affect. A dot probe task will assess for attention bias toward negative or positive stimuli (56). The task will comprise 256 very brief trials (approximately 10 minutes total time) consisting of the various combinations of probe type (the letter E or F), probe position (top or bottom), and emotion type (Neutral, Positive, Negative). The stimuli used for this task will be from the same sets of standardized sets of emotional and neutral words used in our pilot project. During the task, gaze will be monitored using a Tobii Pro Nano mobile eye tracker. Each trial begins with a fixation cross that remains on the screen until the participant makes a fixation on the cross. Then, an emotional-neutral word pair is shown on the screen for 500 ms. After this, a probe (E or F) appears in the location of one of the words. The probe remains on the screen until the participant identifies which letter appeared and presses the corresponding button on the keyboard. To facilitate comparison with previous research, we will compute standard attention bias scores reflecting the difference in reaction times to probes following emotional versus neutral words. However, given concerns about reaction time-based indices of attentional bias (57-60), our primary analyses will be indices of initial orienting (location and latency of first fixation) and sustained attention (overall gaze duration) derived from eye-tracking, which have stronger psychometric properties (58, 59). We will also assess attention to PA using the IPANAT (49). This is an indirect assessment of automatic activation of affective representations that utilizes artificial words paired with positive and negative words. Factor analyses of ratings yield two independent factors interpreted as positive and negative. A single score of implicit affect (positive, negative) reflects both state and trait variance. The IPANAT has demonstrated strong convergent and discriminant validity, and adequate internal consistency and test-retest reliability. A series of experiments found a strong trait component (r = .60) but also susceptibility to environmental changes (e.g., affect induction) and is strongly associated with transient explicit PA and NA. Our two proposed tasks to be administered at baseline, 3-, and 6-month f/u, can assess our primary mechanism of PA, as well as our secondary mechanism of NA.

Subjective Positive and Negative Affect. Self-report ratings of PA and NA will be assessed at baseline, 3-, 6-, and 12-month f/u, through the *Modified Differential Emotions Scale* (mDES)(25). The 19-item mDES assesses short-term state positive and negative emotions, along a 5-point Likert scale. Each item consists of three related terms to describe a particular discrete emotion (e.g., glad, happy, joyful). Participants will be asked to rate each set of emotions based on how they were feeling “right now.” The Positive Emotions subscale is a composite of 10 items, while the Negative Emotions subscale is a composite of 9 items. The scale has psychometric support (25) and in the pilot sample, Cronbach’s α was = .86 and .92 for the positive and negative emotions subscales, respectively. To obtain subjective indices of eudemonic (i.e., sustainable) positive affect, we will administer the *Gratitude Questionnaire* (*GQ6*) (61, 62) and the *Satisfaction with Life Scale* *(SWLS)* (63). Both scales use a 7-point Likert response format and will be administered only to the adolescent.

Ancillary Treatment. To assess ancillary treatment, we will administer the Child and Adolescent Services Assessment Screen (CASA) which is a self-report measure at 3-, 6-, and 12-month follow-up, and administer the Treatment History Interview and the Medication Compliance Questionnaire (MCQ), both interviews, at baseline and 3-, 6-, and 12-month follow-up.

Implementation. Implementation Evaluation is based on Proctor et al.’s (64) categorization of implementation outcomes. This study will measure: 1) acceptability, or the extent to which adopting STEP is agreeable, palatable, or satisfactory among key stakeholders, 2) appropriateness, the perceived fit, relevance or compatibility of STEP for a given setting, provider or family; and 3) feasibility, the extent to which STEP can be successfully used or carried out within a given setting. These will be examined using the Acceptability of Intervention Measure (AIM), Intervention Appropriateness Measure (IAM), and the Feasibility of Intervention Measure (FIM), after all post-treatment data have been collected (65). Each are 4-item scales that have demonstrated good psychometric properties including good test-retest reliability and discriminant validity (65).

In addition we will supplement these measures with qualitative interviews with key stakeholders, until thematic saturation is reached (66), to further explore potential barriers to use of STEP in preparation for a future hybrid effectiveness-implementation trial. As part of study participation, patients and the providers are approached about taking part in an exit interview about the STEP program at the end of their participation at the 12-month follow-up. For those who participated in the pre-implementation interviews, they consented to the exit interview at that time. For stakeholders who only participate in the exit interviews, they will sign a consent to participate in the exit interview. The same consenting process will be used with frontline staff who will be approached either at the end of their participation in the trial (e.g. they take a new position), or after the last participant assigned to them to receive the STEP protocol. Persons in leadership positions will be approached in Year 4 after the last randomized participant has completed the STEP intervention. [name] will supervise the Research Assistants, who will conduct interviews at the conclusion of the intervention with a variety of stakeholders including 15-20 patients, 15-20 parents, 8-10 front line providers who participated in STEP, and 8-10 people serving in clinical and operational leadership positions. Additionally, after each taped interview, field notes will be written to capture other important aspects of the interview. NVivo will be used for the analyses (67).

Data from the survey measures will provide descriptive information on stakeholders’ perspectives and will be integrated with qualitative data, for an exploratory sequential mixed methods analysis of implementation outcomes resulting from the STEP trial (68). Our qualitative data analysis will involve a directed content analysis approach (69) constructed from an *a priori* framework of codes originating from the Proctor Implementation Outcomes Framework (64). Each set of notes will be analyzed by [name] and one RA independently and then compared, as currently used in one of [name] current studies (NIMH R34 MH113598). This early coding will be presented at a research team meeting with subsequent discussions as to whether specific passages from the interview notes represent the concepts of implementation outcomes, as defined by Proctor et al., or other emergent concepts. Consensus on the reliability and validity of this coding will be achieved through this discussion. The analytic team will then proceed to code the remaining interview notes, with discussion and consensus after every coding completion.

